## Abstract

**Background:**

While the efficacy of cognitive therapy (CT) has been well established for social anxiety disorder (SAD) in several randomized controlled trials, there are still large differences between trials with respect to effect sizes. The present study investigates the question of whether enhanced training and the use of behavioral experiments (BEs) increases the efficacy of traditional CT, based on verbal methods of cognitive restructuring.

**Methods/design:**

A mixed within/between conditions design will be applied, with therapists and patients being randomly allocated to one of two conditions: (1) training of CT plus BEs, (2) training of CT “as usual”.

Sixty patients with the primary diagnosis of SAD will be recruited and treated in the outpatient clinic of the Department of Psychology, University of Frankfurt. To ensure adherence to therapist protocols, all therapists will be trained and supervised by the project coordinators. In addition, videotaped treatment sessions will be independently evaluated to guarantee both adherence to protocols and the quality of the intervention. Treatment effects will be assessed by independent SAD symptom ratings using the Liebowitz Social Anxiety Scale as the primary outcome measure and self-report measures as secondary outcome measures.

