### Hypotheses

The present study aims to investigate whether the enhanced implementation of BEs will improve the efficacy of CT for SAD. This goal will be achieved by the following measures:
comprehensive training of the therapists’ competencies in conducting in-session BEs, including self-practice and self-reflection,encouraging therapists to implement this intervention as the major component of the treatment in continuous supervision,establishing double hour sessions to ensure an appropriate setting for BEs.

The experimental condition (CT plus enhanced BEs) will be compared to standard CT as the control condition. An active control condition has been chosen as comparator to control for specific effects of conventional components of cognitive therapy. In standard CT, therapists’ training, supervision, and settings are arranged with a focus on traditional cognitive restructuring techniques.

In a randomized controlled trial, the following major hypothesis will be tested:*Hypothesis 1: As compared to standard CT, CT plus enhanced BEs will result in a significantly higher rate of responders at (a) post-treatment and (b) follow-up.*

The secondary objective is to identify differences in the process of therapy and their association with treatment outcomes. The process-related variables to be assessed include the following therapist variables: general and treatment-specific competencies, and adherence to and allegiance with the treatment manual. The patient variables and treatment outcomes are: changes in insight in SAD-related beliefs, cognitions, avoidance, and symptoms, as well as comorbid depressive symptoms.*Hypothesis 2: In the CT plus enhanced BEs, as compared to standard CT, therapists will show higher levels of adherence related to BEs, and significantly higher levels of allegiance with the treatment approach.**Hypothesis 3: In CT plus enhanced BEs, as compared to standard CT, changes in SAD-related insights, cognitions, avoidance, and symptoms (a) from baseline to post-treatment, and (b) from baseline to follow-up will be significantly increased.*

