### Outcome Measures

The primary outcome measure is treatment response between baseline and posttreatment as assessed by the improvement item of the Clinical Global Impression Scale (CGI) modified for individuals with social anxiety disorder [21]. The CGI is a standard primary outcome measure in psychopharmacologic studies and has two components. The CGI-Severity (CGI-S) contains a Severity of Illness item that provides information about the current severity of social phobic symptoms. The severity rating is made by a clinician on a seven-step categorical scale with 1 representing “normal” or “not at all ill” and 7 representing “among the most severely ill patients”. The CGI-Improvement (CGI-I) rates the change in symptom severity and impairment from the baseline, ranging from 1 (“very much improved”) to 7 (“very much worse”). The psychometric properties of CGI have been found to be very good [5, 22]. The clinical raters assigned to each treatment condition will complete CGI-S at pre-treatment and CGI-I at post-treatment and 6-month follow-up assessment. Patients rated 1 or 2 (markedly or moderately improved from baseline) will be classified as responders, and those rated 3 or higher will be classified as non-responders.

The secondary outcome measures will be changes in the clinician-rated Liebowitz Social Anxiety Scale (LSAS) [23] and the patient-rated Social Phobia Inventory (SPIN) [24] from baseline to post-treatment. The LSAS assesses fear in and avoidance of 24 social situations in the last week, rated on 4-point scales ranging from 0 (non and never) to 4 (severe and usually) of. In the current study we will use the total score by summing both subscales. The SPIN consists of 17 items evaluating fear, avoidance, and physiological discomfort in the last week on a 5-point rating scale, ranging from 0 (not at all) to 4 (extremely). The total score is obtained by adding up the answers of the individual items.

Changes in insight in SAD-related beliefs from baseline to post-treatment and follow-up assessment will be assessed using the German version of the clinician-administered Brown Assessment of Beliefs Scale (BABS) [25–27]. The scale consists of seven items rating the degree of conviction and insight of beliefs from 0 to 4. The outcome measure will be the total score of the first six items.

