## Statistical Procedures

### Analysis of Outcome Variables

The primary outcome measure of the study is the proportion of treatment responders at post-treatment rated by the CGI-I. We dichotomize the variable so that treatment responders are defined by a rating of 1 or 2 (markedly or moderately improved from baseline) and non-responders by a rating of 3 or higher [5, 22]. The secondary outcome variables are changes in the mean scores of LSAS and SPIN from baseline to post-treatment. In addition, the primary and secondary outcome variables will be analyzed at 6-month follow-up to examine changes from baseline to follow-up assessment.

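### The Abstract names the LSAS as the primary outcome; the body names CGI-I response at post-treatment and makes the LSAS secondary

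*Protocol article*

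**What the plan says.** **Abstract, Methods/design.** "Treatment effects will be assessed by independent SAD symptom ratings using the Liebowitz Social Anxiety Scale as the primary outcome measure", with self-report measures as secondary outcomes. The CGI is not mentioned there and no time point is given.

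**Outcome Measures.** "The primary outcome measure is treatment response between baseline and posttreatment as assessed by the improvement item of the Clinical Global Impression Scale". Ratings of 1 or 2 count as response. The LSAS and the SPIN are placed among the secondary measures.

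**Analysis of Outcome Variables.** "The primary outcome measure of the study is the proportion of treatment responders at post-treatment rated by the CGI-I". Then: "The secondary outcome variables are changes in the mean scores of LSAS and SPIN from baseline to post-treatment". The 6-month follow-up is introduced afterwards as an additional analysis of both sets of outcomes.

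**Statistical Analyses.** The CGI-I is again called the primary measure, to be compared by chi-square or Fisher's exact test. In the ITT analysis of response, drop-outs count as failures. Dimensional measures, which include the LSAS, go to ANCOVA adjusted for the pre-treatment score, with last observation carried forward.

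**Hypotheses.** The one major hypothesis concerns responders: "CT plus enhanced BEs will result in a significantly higher rate of responders at (a) post-treatment and (b) follow-up".

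**Design and Sample Size.** d = 0.60, f = 0.35, 90% power, two-sided alpha 0.05, N = 54, raised to 60 for 10% drop-out. No outcome is named and no responder rates are given.

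**The concern.** A trial's primary outcome should read the same wherever it appears. Here the most widely read part of the article names one measure and the methods name another, and no unseen analysis plan can make both statements true. Nor is this a matter of an abstract being condensed: it ranks the LSAS as primary where the body ranks it as secondary.

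The two candidates differ in scale (continuous or binary), in test, and in the handling of patients who leave treatment. In 60 patients one can reach significance without the other. If that happened, either result could be presented as the pre-specified answer with a sentence of the published protocol to support it, and the nominal 5% error rate would no longer describe the claim.

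**Working it through.** **1. The statements side by side**

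| Place | Primary | LSAS | Time point of primary |
|---|---|---|---|
| Abstract | LSAS | primary | not given |
| Hypotheses (H1) | responder rate | – | post-treatment and follow-up |
| Outcome Measures | CGI-I response | secondary | post-treatment |
| Analysis of Outcome Variables | CGI-I response | secondary | post-treatment; follow-up additional |
| Statistical Analyses | CGI-I | not named; falls under dimensional measures | – |

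One sentence, in the Abstract, stands against the rest. The sections that define the outcomes and the analysis agree with each other.

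**2. Does the sample size show which outcome was meant?**

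The only figure to reproduce is N = 54. For a difference in means, n per arm = 2(z₀.₉₇₅ + z₀.₉₀)²/d² = 2(1.960 + 1.282)²/0.60² = 58.4, so 59 per arm (60 with the exact t distribution), or 118–120 in total. The stated 27 per arm is not reached. It appears under baseline-adjusted ANCOVA only with a baseline correlation of about 0.74, which the article does not state. The drop-out step does reproduce: 54/0.9 = 60.

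For CGI-I response no calculation can be reproduced, because no rates are given. As an assumption only, converting d = 0.60 to an odds ratio gives exp(0.60 × π/√3) = 2.97. With control response between 30% and 66%, power at 27 per arm is then about 37% to 50%, against 58% (t) to 60% (normal approximation) for a mean difference of d = 0.60.

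So the stated calculation matches neither outcome on its stated inputs and names neither. It cannot serve as a tie-breaker. The shortfall in N is a separate matter and is not argued here.

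**3. Error rate if either outcome may be called primary**

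Inputs: two tests, each two-sided at 0.05 (Statistical Analyses); no true difference; correlation r between the two test statistics, which the article does not give and is therefore assumed. With (Z₁, Z₂) bivariate normal,

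P(at least one significant) = 1 − P(|Z₁| < 1.96 and |Z₂| < 1.96).

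| r | At least one significant |
|---|---|
| 0.3 | 9.5% |
| 0.5 | 9.1% |
| 0.7 | 8.3% |
| 0.9 | 7.0% |

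The limit under independence is 1 − 0.95² = 9.75%.

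**4. Effect of the choice between chi-square and Fisher**

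The table treats both tests as having exactly 5% size. At 30 per arm with a common response rate of 30–66%, the uncorrected chi-square test has true size of about 0.05, but Fisher's exact test only about 0.026. Repeating step 3 with 0.026 for the CGI-I test gives 7.0% (r = 0.5) and 6.5% (r = 0.7). The 8–9% therefore belongs to the chi-square option; with Fisher the inflation is smaller but still present.

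**The case against.** The strongest reply is that the plan is not undecided. The major hypothesis is about responders, Outcome Measures and Analysis of Outcome Variables both make CGI-I response primary, and Statistical Analyses repeats it. A careful reader would take the Abstract sentence as a slip. Most of this stands. It limits the point to a mismatch between Abstract and body, and it shows which way to correct it. It does not remove the contradiction.

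Some stronger readings are tempting and are not supported:

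- **That the deciding time point is open because H1 lists two.** Outcome Measures and Analysis of Outcome Variables both fix the primary outcome at post-treatment, and the latter adds follow-up as a further analysis. If H1 required both time points, the error rate would not exceed 5%. What remains is that H1 does not label its second part.
- **That two outcomes at two time points make four rival primaries, with a correspondingly larger error rate.** Nothing in the article makes the LSAS at follow-up primary.
- **That the use of d and f shows the LSAS was intended.** The calculation names no outcome.
- **That the two outcomes will probably disagree.** With no true effect and each test at 5%, exactly one is significant in 2 × 9.1% − 10% = 8.2% of trials at r = 0.5, and in 2 × 8.3% − 10%, about 7%, at r = 0.7. Disagreement is possible, but it is not the expected result.
- **That the body settles the analysis set.** All analyses are to be run on the ITT and completer samples, and neither is named as primary.

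**Conclusion.** The contradiction is real and concerns the trial's defining outcome, so it must be corrected. It is confined to the Abstract against a consistent body. The cost of leaving it is an error rate of about 8–9% rather than 5%, conditional on three things: success may be claimed on either outcome, each test is at its nominal 5% size, and the correlation between the test statistics is 0.5–0.7 (7.0–9.5% over 0.9–0.3). If CGI-I response at post-treatment alone decides, as the body says, the rate stays at 5%. The unlabelled follow-up part of H1 is a minor point of wording.

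**What to change.** Before outcome data are analysed:

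1. Correct the Abstract so that CGI-I response (rating 1 or 2) at post-treatment is the single primary outcome and the LSAS is secondary.
2. Check that the registry entry carries the same outcome and time point. It was not available for this review.
3. In H1, label part (b), follow-up, as secondary, in line with Analysis of Outcome Variables.

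The cost is a few words in the Abstract and one label in H1. The article gives the trial status as recruiting. No change to design, data collection or analysis method is needed for this point.

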**Discussion:**

The present cognitive behavioral therapy (CBT) trial will be the first to clarify the contribution of BEs to the efficacy of CT in a randomized controlled design. Study results are relevant to clinical training and implementation of evidence-based treatments.

**Trial registration:**

German Clinical Trials Register International Clinical Trials Registry Platform (ICTRP) identifier: DRKS00014349. Trial status: recruiting.

## Background

Social anxiety disorder (SAD) is a highly prevalent and chronic psychiatric disorder associated with considerable psychosocial impairment. In recent years, growing evidence has suggested that individual cognitive therapy (CT) based upon the Clark and Wells model [1] may be superior to some alternative cognitive behavioral therapy (CBT) approaches, as well as to other treatment modalities. Six randomized controlled trials in three different countries have compared individual CT with alternative active treatments; individual CT was proven to be significantly more effective. Individual CT outperformed two versions of group CBT [2, 3], in vivo exposure [4], interpersonal psychotherapy [5], psychodynamic short-term psychotherapy [6], fluoxetine plus self-exposure instructions [4], and medication-based treatment as usual [3]. Mayo-Wilson et al. [7] reported a network meta-analysis of 101 randomized controlled trials on 41 psychological and pharmacological treatments and again demonstrated the highest effect sizes for Clark & Wells’ individual CT and a related individual CBT developed by Heimberg and colleagues.

Although the finding that individual CT is superior to other comparable treatments is consistent across studies in three European countries, Mayo-Wilson et al. [7] found that there was a significant difference in the magnitude of within CT change between English trials [4] [8] and German [2, 5, 6] and Swedish [3] trials. The standard mean difference compared to no treatment was − 1.56 for the English trials and − 0.97 for the German and Swedish trials.

There are several possible factors that may account for the differences between the two sets of trials. First, when comparing trials against the Clark et al. ones, the allegiance to the treatment may differ between researchers and therapists. Although the influence of researcher allegiance was minimized by the inclusion of D.M. Clark in the training, implementation and publication of the data of all trials, there are no data that allow for a direct comparison of therapist allegiance. Second, in the English trials almost all sessions were 90 min long to arrange the implementation of out of office behavioral experiments; however, in the German and Swedish trials, most therapists used shorter sessions lasting 50 min, which is in line with healthcare standards, but provides insufficient time to effectively set-up and discuss the results of in-session behavioral experiments. Evidence in support of this concern comes from a recent analysis [9] of video tapes and therapist protocols of CT treatments from the SOPHONET trial, a large-scale multicenter randomized controlled trial [6] comparing the efficacy of CT and short-term psychodynamic psychotherapy in Germany. Therapists protocols from *N* = 165 completed treatments disclosed which treatment interventions were actually applied in the sessions. Results indicated that almost all therapists applied basic cognitive interventions, such as deriving a cognitive model, roleplaying to avoid safety behaviors and self-attention, video feedback, and verbal techniques of cognitive restructuring (e.g., Socratic dialogue). In contrast, the frequency of behavioral experiments (BE) was significantly reduced compared to the required standard in the manual (the mean frequency in treatment was 1.7, versus a mean recommended frequency of 6). Furthermore, the analysis of the duration of the sessions revealed that the vast majority of sessions (on average 17 out of 25) lasted only 50 min. This indicates that the preference for 50-min sessions, as is usual in healthcare for psychotherapy settings, may have been one of the reasons for the low rate of BEs in the study.

However, there is some evidence that BE is a major effective component of CT. For instance, [10] found evidence that BE involving safety behaviors, attention manipulation, and video feedback are more effective in the treatment of SAD than traditional exposure. Thus, a possibly major effective component of CT was not implemented in the German trials and this failure may account for the differences in the effect sizes. However, as of yet, there is no direct evidence showing that the systematic use of BEs has a significant impact on the outcomes achieved with CT.

Given the possibility that the large differences in the effect sizes found for CT based on the Clark & Wells model may account for different amounts of BEs, there is an additional need to clarify the reasons for the insufficient implementation of BEs. Two factors may be responsible for the lack of adherence with this component of CT:
Lack of specific competence:

There is evidence that higher levels of general therapist competence are associated with better outcomes [9, 11]. In addition, Stangier et al. [9] found that in the SOPHONET trial, the specific competence to conduct BEs was significantly correlated with outcome (*r* = 0.28). Thus, training and supervision might have been insufficient to deliver adequate skills to plan and implement BEs as a routine component of CT.
2.Lack of therapists’ allegiance:

Although in vivo exposure has been proven to be an effective therapy for anxiety disorders, the majority of behavioral therapists in healthcare do not apply this method [12, 13]. There is evidence that one reason for the underutilization of exposure is negative beliefs about its effects [14]. In the context of BEs, negative expectations of their outcomes may have prevented therapists from conducting interventions. Although generally the outcomes of BEs will differ from the extreme expectations of patients, and even though the processing of negative results can be restructured upon subsequent reflection, therapists might prefer interventions with a lower risk of failure.

To summarize, the lack of specific competence and allegiance with BEs may account for the insufficient implementation of BEs and the lower efficacy of CT in the trials conducted in Germany compared to the trials conducted by the Oxford/London group. Consequently, intense training, the supervision of specific competencies, enhancing allegiance with this approach by including self-practice/self-reflection [15] in its training and establishing an appropriate setting (prolonged sessions, in situ guidance) to implement BEs is expected to significantly improve Standard CT.

### Hypotheses

The present study aims to investigate whether the enhanced implementation of BEs will improve the efficacy of CT for SAD. This goal will be achieved by the following measures:
comprehensive training of the therapists’ competencies in conducting in-session BEs, including self-practice and self-reflection,encouraging therapists to implement this intervention as the major component of the treatment in continuous supervision,establishing double hour sessions to ensure an appropriate setting for BEs.

The experimental condition (CT plus enhanced BEs) will be compared to standard CT as the control condition. An active control condition has been chosen as comparator to control for specific effects of conventional components of cognitive therapy. In standard CT, therapists’ training, supervision, and settings are arranged with a focus on traditional cognitive restructuring techniques.

In a randomized controlled trial, the following major hypothesis will be tested:*Hypothesis 1: As compared to standard CT, CT plus enhanced BEs will result in a significantly higher rate of responders at (a) post-treatment and (b) follow-up.*

The secondary objective is to identify differences in the process of therapy and their association with treatment outcomes. The process-related variables to be assessed include the following therapist variables: general and treatment-specific competencies, and adherence to and allegiance with the treatment manual. The patient variables and treatment outcomes are: changes in insight in SAD-related beliefs, cognitions, avoidance, and symptoms, as well as comorbid depressive symptoms.*Hypothesis 2: In the CT plus enhanced BEs, as compared to standard CT, therapists will show higher levels of adherence related to BEs, and significantly higher levels of allegiance with the treatment approach.**Hypothesis 3: In CT plus enhanced BEs, as compared to standard CT, changes in SAD-related insights, cognitions, avoidance, and symptoms (a) from baseline to post-treatment, and (b) from baseline to follow-up will be significantly increased.*

An additional objective is to identify outcome predictors, including therapist and patients’ variables and the therapeutic relationship.*Hypothesis 4:**The following variables are expected to predict positive treatment outcomes:**Therapist variables: competencies, adherence, and allegiance; therapist-rated therapeutic relationship**Patient variables: preferred learning style at pre-treatment, changes in insights in SAD-related beliefs, changes in SAD-related cognitions; patient-rated therapeutic relationship.*

## Methods/Design

### Design and Sample Size

The design of the study is a between group design with two treatment groups (CT plus enhanced BEs, standard CT). Patients will be randomly allocated to one of the two groups. The outcome criteria will be assessed by blinded independent raters at pre-treatment, post-treatment, and at follow-up 6months after post-treatment and treatment termination (Fig. 1).

